## Methods

### Study design

This is a multicenter subject-blinded randomized controlled trial comparing EA with sham EA. Five hundred women with pure SUI will be recruited from the following 12 hospitals in China: Guang’an men Hospital of China Academy of Chinese Medical Sciences (CACMS); Xiyuan Hospital of CACMS; Dongzhimen Hospital affiliated to Beijing University of Chinese Medicine; Yueyang Hospital of Integrated Traditional Chinese and Western Medicine affiliated to Shanghai University of Traditional Chinese Medicine (TCM); West China Hospital of Sichuan University; First Teaching Hospital of Tianjin University of TCM; First Hospital of Hunan University of Chinese Medicine; Hengyang Hospital affiliated to Hunan University of Chinese Medicine; Hubei Provincial Hospital of TCM; Jiangsu Province Hospital of TCM;, Shanxi Province Hospital of TCM; and Shanxi Hospital of Integrated Traditional and Western Medicine. Participants will be randomly assigned (on a 1:1 ratio) to the EA group or the sham EA group by a central randomization system performed by the Clinical Evaluation Center of the CACMS in Beijing. The randomization sequence will be generated by the ‘proc plan’ procedure of the SAS9.3 analytic software according to center-stratified, block randomization with a block size of six. Random number and group assignment will be offered by telephone, mobile phone, or website from the Clinical Evaluation Center of the CACMS. In this study, participants, outcome assessors, and statisticians will be blinded to treatment allocation. The flowchart and study design schedule are presented in Figure 1 and Table 1, respectively.

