### Statistical methods

#### Sample size calculation

We conducted a pilot study comparing the effects of deep EA with shallow EA on women with SUI in Guang’an men Hospital of CACMS between June 2011 and February 2012. Results from our pilot study revealed that: compared with the baseline, the volume of urine leakage from the 1-h pad test decreased by 2.10 g, with a standard deviation of 2.26, after 4 weeks deep EA treatment, and by 0.64 g with a standard deviation of 0.97 after 4 weeks shallow EA treatment [16]. We performed sample size calculation according to results of our pilot study because no placebo control trial has been reported. A sample size of 117 in each group will be sufficient to detect a clinically important difference of 1 g on the volume of urine leakage from a 1-h pad test, assuming a standard deviation of 2.61 (considering a larger variability in multicenter trial, the pooled standard deviation of pilot study 1.74 was expanded by 1.5 times), using a one-tailed *t*-test of the difference between means, a significance level of 5%, and a power of 90%. The calculation is based on the assumption that measurements on volume of urine leakage from a 1-h pad test are normally distributed. This number has been increased to 140 per group (total of 280), to allow for a predicted drop-out rate of 20%. As our pilot study had a small sample size (*n*=40) and as we will undertake subgroup analysis, we expanded the sample size to 500 cases (250 cases in each group) to enhance the reliability of the study.

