#### Statistical analysis

Statistical analysis will be performed by the Clinical Evaluation Center of CACMS in Beijing and the Department of Biostatistics, University of Washington, Seattle, United States. The statistician will be blinded from the allocation of groups. PASW Statistics 20.0 and SAS9.0 statistical software will be used for data analysis. The level of significance is established at α<0.05 with a two-tailed test.

The main objective is to compare the change in the amount of urine leakage at week 6 from the baseline between the treatment group and the control group. The null hypothesis is that the treatment group has the same change as the control group, while the alternative hypothesis is that the treatment group shows a greater decrease.

Continuous data will be represented by the average, standard deviation, median, minimum value, and maximum value, whereas categorical data will be represented by percentages. For comparison with the baseline, a *t*-test or non-parametric test will be used for continuous data, and non-parametric tests for categorical data. For comparison of two independent samples: if the residual are normally distributed, the analysis of covariance (ANCOVA) will be used for the primary outcome and subgroup analysis stratified by incontinence severity, a *t*-test for other continuous data, and a chi-square test for categorical data; if the residual are abnormally distributed, a non-parametric test will be used for both continuous and categorical date. Detailed contents and methods are as follows.

1. Case distribution and compliance analysis: The case distribution of both groups in every center will be described. The total drop-out rate and the drop-out rate due to adverse events, of both groups, will be compared using Fisher’s exact test.

2. Analysis of baseline characteristics.

3. Analysis of compliance: The implementation of protocol intervention will be compared between the two groups. Compliance will be evaluated according to the case report forms.

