4. Analysis of efficiency: Intention-to-treat (ITT) analysis will be used to assess the validity of the study. Efficiency analysis will be based on the ITT population which is defined as all randomized participants. Missing data and non-compliance data will be included in the efficiency analysis. Missing data, from subjects without any treatment after randomization, or without any valid data of evaluation although treated, will be analyzed by multiple imputation by the inverse probability weighting method. Non-compliance data will be analyzed by the instrumental variable.

5. Analysis of primary outcome: In this study, we will use the change in the amount of urine leakage at week 6 from the baseline as the primary outcome. To adjust for baseline imbalance, a comparison of the decreased value of urine leakage between the groups will be done by ANCOVA using baseline and centers as covariates, when the residual are normally distributed. Meanwhile, a covariance model including interactions between centers and group will be made to analyze the center effect. Causes will be further analyzed if any center effect is identified. Comparison of decreased value of urine leakage between groups will be analyzed by a non-parametric test if the residual are abnormally distributed with neglect of baseline balance.

6. Analysis of secondary outcomes:

A 72-h incontinence episode frequency (IEF), the International Consultation on Incontinence Questionnaire-Urinary Incontinence (ICIQ-UI) Short Form score, and weekly consumption of pads of weeks 6, 18, and 30 will be compared with their respective baselines, and a *t*-test or non-parametric test will be used for comparison among groups.

For severity of urinary incontinence based on a 72-h bladder diary and a self-report assessment of therapeutic effect, the case number and percentage of each rank of weeks 6, 18, and 30 will be compared with their baselines, and a chi-square test or non-parametric test will be used for comparison among groups.

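### A residual-normality check picks the primary test, and the likely fallback gives up baseline adjustment and the mean difference in grams on which the trial is sized

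*Protocol article*

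**What the plan says.** The primary outcome is the change in 1-h pad test leakage from baseline to week 6. Item 5 of Statistical analysis gives both the method and its purpose: "To adjust for baseline imbalance, a comparison of the decreased value of urine leakage between the groups will be done by ANCOVA". The model is "ANCOVA using baseline and centers as covariates, when the residual are normally distributed". If residuals are not normal, the comparison "will be analyzed by a non-parametric test if the residual are abnormally distributed with neglect of baseline balance".

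The opening paragraphs of the same section state the switch as a general rule for comparing two independent groups: "if the residual are abnormally distributed, a non-parametric test will be used for both continuous and categorical date".

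Two other places bear on this. Study design describes "center-stratified, block randomization with a block size of six" over 12 hospitals. Sample size calculation is built on a 1 g difference between means and says "The calculation is based on the assumption that measurements on volume of urine leakage from a 1-h pad test are normally distributed".

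**The concern.** The single confirmatory test depends on a look at the trial's own residuals. Three things follow if the check fails.

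- **Baseline adjustment is given up.** Residual shape has no bearing on whether a chance baseline imbalance needs adjusting for, so the fallback abandons the plan's own reason for ANCOVA without cause.
- **The target changes.** The trial is sized to detect 1 g between means. A rank-type test asks a different question and yields no baseline-adjusted difference in grams.
- **Centre is not mentioned.** The randomisation stratum is in the ANCOVA but is not named in the fallback.

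This would matter little if the fallback were a remote contingency. The question is therefore how likely it is, and what is lost when it applies.

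**Working it through.** **1. The plan's own figure.** Pooled pilot SD = √[(2.26² + 0.97²)/2] = √3.024 = 1.74, and 1.74 × 1.5 = 2.61. For 1 g, one-sided 5% and 90% power: n = 2 × (1.645 + 1.282)² × 2.61² / 1² = 116.7, so 117 per group, as stated. The planning quantity is a difference between means.

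**2. How likely is the switch?** Inputs: pilot SDs 2.26 (deep EA) and 0.97 (shallow EA), from Sample size calculation.

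- Variance ratio = (2.26/0.97)² = 5.43.
- Scaled by the protocol's 1.5, the SDs are 3.39 and 1.455.
- Even if each arm is exactly normal, the pooled residuals mix two spreads. Their kurtosis is 3 × [(2.26⁴ + 0.97⁴)/2] / [(2.26² + 0.97²)/2]² = 3 × 13.486/9.146 = 4.42, against 3 for a normal distribution.
- With 250 × 0.8 = 200 evaluable per arm (400 residuals), the standard error of kurtosis under normality is about √(24/400) = 0.245. The excess of 1.42 is about 5.8 standard errors.
- In simulation with Shapiro-Wilk at 5% (an assumed check), the switch occurred in 87% of trials at 117 per arm, about 98–99% at 200 and 99.6% at 250. No skewness was assumed; skewed pad weights would make the switch more likely still.

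**3. What happens to power on the planning figures?** Two-sided 5%, 200 per arm, 1 g:

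| Setting | Analysis | Power |
|---|---|---|
| Normal, SD 2.61 | unadjusted t-test | 96.9% |
| Normal, SD 2.61 | unadjusted rank test (efficiency 0.955) | 96.3% |
| Normal, baseline–change correlation 0.3 / 0.5 (assumed) | ANCOVA | 98.0% / 99.3% |
| Normal, SDs 3.39 and 1.455 | t-test / rank test | 96.9% / 95.0% |

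In the last setting, type I error was about 6.3% for the rank test and 5.0% for the t-test. That excess comes from the unequal variances, not from switching.

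**4. Skewed data.** Assumed: lognormal pad weights, 25% reduction in leakage, 200 per arm; rho is the baseline-to-week-6 correlation on the log scale.

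| Log-SD, rho | ANCOVA, robust (HC3) SE | Unadjusted rank test on change | Baseline-adjusted rank ANCOVA |
|---|---|---|---|
| 0.8, 0.5 | 92% | 88% | 96% |
| 1.2, 0.7 | 50% | 73% | 80% |

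The order of the first two columns reverses as skew grows. The third column beats the second in both rows.

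**5. The switching rule itself.** In four further assumed shapes with 12 centres and 200 per arm, the two-stage rule had type I error of 4.5–4.9%. Under the alternative, ANCOVA and the unadjusted rank test gave different significance verdicts in 10–33% of trials.

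**The case against.** The strongest reply is that the rule is written in advance, depends on residual shape rather than on which p-value is smaller, and is applied by a statistician blinded to allocation. That stands: the simulations show no material type I inflation from switching, so this is not a finding of selective testing.

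A reader might also infer that the fallback is the weaker test. The documents do not support that. They give no pad-weight distribution, and the ranking turns on assumed skew (step 4). In the shapes of step 5, the rank test was stronger in two of the three non-normal ones (71% v 50% and 86% v 72%) and weaker in the third (88% v 97%). On the planning figures, 500 participants leave about 95% power or more either way.

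Nor does the text say that centre is dropped, or that the test is a Mann-Whitney test. It says only that the test is non-parametric, and a centre-stratified rank test would fit the wording. Only the loss of baseline adjustment is explicit. It would also be too strong to say that nothing in grams would be reported, because means, SDs and medians are planned as descriptive summaries.

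Finally, the normality check, its cut-off and the name of the fallback test may properly sit in an analysis plan that is not shown. That is so, and their absence is not the finding. The finding is the stated rule: any analysis plan that follows it keeps the switch and the loss of baseline adjustment.

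**Conclusion.** The point holds and should be fixed before unblinding. The protocol lets residual shape decide between two primary analyses with different targets. On its own pilot SDs the second is the more likely to be used, in about 98–99% of trials at 200 per arm. That figure assumes a formal Shapiro-Wilk test at 5%, normal data within arms, and the pilot's variance ratio carrying over. The pilot had 40 participants and compared deep with shallow EA, and a check by eye could decide differently.

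When the switch occurs, baseline information is discarded for no reason, and the result no longer speaks directly to the 1 g mean difference. In the assumed lognormal settings, the cost against a baseline-adjusted analysis of the same kind is 96 − 88 = 8 and 80 − 73 = 7 percentage points of power. No claim is made that the fallback has less power than ANCOVA, or that the switching raises the false-positive rate.

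**What to change.** In item 5, delete the normality condition and the clause giving up baseline balance, and make the general paragraph consistent. Then state:

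- **Primary analysis, whatever the residual shape:** ANCOVA of week-6 change on arm, baseline pad weight and centre, with heteroscedasticity-robust (HC3) standard errors, reporting the mean difference in grams with a 95% CI. With about 200 per arm this does not depend on normal residuals.
- **Prespecified sensitivity analysis:** a rank analysis adjusted for baseline and centre.

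The cost is wording only, with no extra data. No extra participants are needed either: for two-sided 90% power at 1 g and SD 2.61, ANCOVA needs 131 or 108 per group at an assumed baseline–change correlation of 0.3 or 0.5, against 144 for a t-test and about 200 evaluable.

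There is a downside. If pad weights are very skewed, ANCOVA on grams can have less power than a rank analysis (50% v 80% for baseline-adjusted rank ANCOVA in the more skewed setting above). That is the price of keeping the 1 g target. If the sponsor prefers to keep a non-parametric fallback, it must at the minimum be adjusted for baseline and stratified by centre.

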**Secondary outcomes**	
1. 72-h IEF	Evaluated at weeks 6, 18, and 30. The change of average 72-h IEF from the baseline will be analyzed
	Based on a 72-h bladder diary, the average 72-h IEF of week 6 is calculated by averaging the IEF of weeks 2, 4, and 6; values of week 18 and 30 are calculated by averaging IEF of weeks 15–18 and 27–30, respectively
2. ICIQ-UI Short Form score	Evaluated at weeks 6, 18, and 30. The change of score from the baseline will be analyzed
3. Severity of urinary incontinence	Evaluated at weeks 6, 18, and 30. Change in the number and percentage of severity rating from the baseline will be analyzed
	The most severe degree during weeks 2, 4, and 6 will be taken as severity of urinary incontinence of week 6
	The most severe degree during weeks 15–18 and weeks 27–30 will be taken as severity of urinary incontinence of week 18 and week 30, respectively
4. Self-report assessment of therapeutic effect	Evaluated at weeks 6, 18, and 30
	A 4-point scale is used: no help, little help, medium help, and great help
5. Weekly consumption of pads	Evaluated at weeks 6, 18, and 30. The change in average consumption of pads from the baseline will be analyzed
	The pads consumption of weeks 6, 18, and 30 will be calculated by averaging the weekly usage of pads during weeks 1–6, weeks 7–18, and weeks 19–30, respectively
6. Application of other treatment for SUI (including drugs and other specialist treatment)	Evaluated at weeks 6, 18, and 30. The number of patients who used other treatments for SUI during the trial will be analyzed between the two groups
7. Subgroup analysis stratified by incontinence severity	Evaluated at weeks 6, 18, and 30
	Stratified by incontinence severity at the baseline, the correlation between the rating of incontinence severity and the treatment effect will be analyzed. Different outcomes of treatment effect are used in each evaluation: week 6, the change in amount of urine leakage at week 6 from the baseline measured by 1-h pad test; week 18, the change of average 72-h IEF at week 18 from the baseline; and week 30, the change of average 72-h IEF at week 30 from the baseline

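### Two ordered secondary outcomes are left to chi-square or an unnamed non-parametric test, with a residual-normality rule that cannot choose between them for categories

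*Protocol article*

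**What the plan says.** Table 2 of the protocol article lists two secondary outcomes on ordered scales, each evaluated at weeks 6, 18 and 30.

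- **Self-report of therapeutic effect:** "A 4-point scale is used: no help, little help, medium help, and great help".
- **Severity of urinary incontinence**, graded from the 72-h bladder diary: "The most severe degree during weeks 2, 4, and 6 will be taken as severity of urinary incontinence of week 6". Weeks 18 and 30 are handled in the same way. The article does not state the number of grades.

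Item 6 of the Statistical analysis section treats the levels of both outcomes as ranks: "the case number and percentage of each rank of weeks 6, 18, and 30 will be compared with their baselines". It then gives the between-group test as "a chi-square test or non-parametric test will be used for comparison among groups".

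The only rule for choosing stands in the general paragraph of the same section. It opens "For comparison of two independent samples: if the residual are normally distributed" and, for that case, assigns "a chi-square test for categorical data; if the residual are abnormally distributed, a non-parametric test will be used for both continuous and categorical date". No non-parametric test is named. The level is set once for all analyses: "The level of significance is established at α<0.05 with a two-tailed test".

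**The concern.** A normality check on residuals can help to choose between a t-test or ANCOVA and a rank test for a continuous outcome. The protocol extends it to categorical outcomes, where it cannot do that job. Six between-group comparisons (two outcomes at three time points) therefore have two permitted tests and no working rule for choosing.

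The two tests answer different questions. A Pearson chi-square gives the same result however the categories are reordered. A rank or proportional-odds test looks for movement along the scale. The trial's interest is directional, in whether electroacupuncture gives more improvement than sham. At stake are the power to show such movement, on a scale that includes the patient's own judgement of benefit, and a test that is fixed before the data are seen.

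**Working it through.** **1. Can the rule select a test?** A chi-square comparison of two groups on categories produces no residuals to which a normality check applies. Suppose instead that the grades were scored 1, 2, 3, 4 and residuals taken from a linear model. These would fall on a few discrete values and could not be normal, so the rule would always lead to the non-parametric branch and the chi-square branch would be empty. Nor does the label settle it, because Pearson's chi-square is itself commonly classed as non-parametric. On any reading the rule does not choose between the two tests, and item 6 offers no other.

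**2. The plan's own figures.** The protocol states no power for these outcomes. Its sample-size figure concerns the pad test and reproduces: 2 × (1.645 + 1.282)² × 2.61² / 1² = 116.7, hence 117 per group (one-tailed 5%, 90% power). The point does not rest on it.

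**3. Inputs for the power comparison.**
- From the Sample size calculation: 250 per group, or 250 × 0.8 = 200 evaluable with the predicted 20% drop-out.
- From Statistical analysis: two-tailed 5%.
- Assumed, because the article gives none: the sham distribution over four levels (30/30/25/15%), the odds ratios, and 40/40/20% for a three-level case.

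**4. Formulas.**
- Chi-square: X² = Σ(O − E)²/E, with k − 1 degrees of freedom (3 for four levels).
- Rank test: z = (W − n₁(N+1)/2) / √V, where V = (n₁n₂/12) × [(N+1) − Σ(t³ − t)/(N(N−1))] and t is the number tied in each category.
- Proportional shift: each cumulative odds is divided by the odds ratio. For 1.5, 0.30/0.70 = 0.429 becomes 0.286, so the lowest category falls from 30% to 22.2%. The full distribution becomes 22.2/27.8/29.1/20.9%.

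**5. Simulated power.**

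| Levels | Per arm | Effect | Chi-square | Rank test |
|---|---|---|---|---|
| 4 | 250 | OR 1.5 | 54% | 71% |
| 4 | 250 | OR 1.7 | 80% | 91% |
| 4 | 250 | OR 2.0 | 96% | 99% |
| 4 | 200 | OR 1.6 | 57–58% | 74% |
| 3 | 250 | OR 1.5 | 58% | 68% |
| 4 | 200 | 30/30/25/15 to 20/40/25/15 (not proportional) | 58% | 19% |
| 4 | 200 | 30/30/25/15 to 30/20/25/25 (not proportional) | 71–72% | 40% |

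Other assumed four-level sham distributions (flat, skewed low, skewed high, middle-heavy) at 250 per arm and OR 1.5 give 52–54% against 69–71%.

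**6. Analytic check.** For 80% power the noncentrality must be 7.85 with 1 df and 10.90 with 3 df, a ratio of 10.90/7.85 = 1.39. For 90% power it is 14.17/10.51 = 1.35. Where the effect is a consistent shift, the 3-df test thus needs about 1.35 to 1.39 times the sample size. Where the 1-df test has 80% power, chi-square has about 64% with four levels and 71% with three.

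**7. Type I error.** With no treatment effect, each test alone rejects in about 5% of simulated trials. Rejecting when either p-value is below 0.05 gives 7.5% to 8.3% across the settings.

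**The case against.** The strongest reply is that the plan does not prescribe chi-square. It permits a rank test and calls the levels ranks, so a reader may expect a rank test. The exact name of a test for a secondary outcome is also a detail that an article may leave to the full protocol or SAP. That reply disposes of any complaint about missing detail. It does not rescue the rule, which the article states and explicitly extends to categorical data. An SAP written to follow it would inherit the fault.

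The reply also rightly limits the size of the point. The power figures depend on assumed distributions and on proportional odds, which favours the rank test. The last two rows of the table show improvements, every move being to a better category, where chi-square does better. The four-level figures cannot simply be carried over to severity, because its number of grades is not given.

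A reader might infer two stronger points, and the document supports neither.

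- **That the false-positive rate exceeds 5%.** This needs the test to be picked by its p-value. The plan does not say so, and it blinds the statistician to allocation, which makes a biased choice less likely.
- **That both permitted tests ignore the centre-stratified randomisation.** The non-parametric test is unnamed, and a centre-stratified rank test would fall within the wording.

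**Conclusion.** The point holds in a limited form. The residual-normality rule cannot be applied to categorical outcomes, so the test for two ordered secondary outcomes is not fixed, and one permitted option discards the ordering. If chi-square is used and the true effect is a roughly proportional shift, the loss with four levels is about 17 percentage points of power at a moderate effect (OR 1.5, 250 per arm) and about 3 points at a large one (OR 2.0). It is smaller with three levels and can reverse for other shapes of effect. The figures rest on the assumed distributions and odds ratios shown above. About 8% type I error is an upper bound under selection by p-value, not a property of the plan. The primary outcome, analysed by ANCOVA or its non-parametric alternative, is untouched. The change is worth making but is not critical.

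**What to change.** In the Statistical analysis section, confine the residual-normality rule to continuous outcomes. In item 6, replace the open choice for severity and self-report with one ordinal method, named in advance and used for both outcomes at weeks 6, 18 and 30. It should preferably be stratified by centre, to match the randomisation. Two suitable options are:

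- a van Elteren test (Wilcoxon stratified by centre), which gives a test but no common odds ratio; or
- a proportional-odds model with treatment and centre, reporting the common odds ratio with its confidence interval.

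Keep chi-square or Fisher's exact test for binary and nominal items.

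The cost is a few lines of wording and no new data. The small statistical downside is lower power for non-monotone or strongly non-proportional differences. Reporting the full category counts by arm, which item 6 already foresees, lets a reader see such a pattern.
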